## Intervention: the OPEN AOS model

The OPEN AOS model provides emergency substitution care to older adults residing in RACFs located within the MNHHS catchment area. Nurse-led and physician supported, OPEN AOS commenced in January 2022 and became fully operational by June 2022. The service is based in office space adjacent to a MNHHS hospital and operates 12 h per day between the hours of 08:00–20:00, Monday to Sunday. The service aims to (i) decrease the time to treating emergency clinician and (ii) reduce the number of avoidable ambulance transports to ED for older adults living in RACFs. The OPEN AOS model is staffed by 3.0 full-time equivalent (FTE) Nurse Practitioners^1^ (NP); 1.0 FTE NP candidates (NPC)^2^; and 1.8 FTE RNs^3^ [40, 41]. The model is supported by 1.4 FTE Senior Medical Officers (SMO)^4^ [42, 43] and 0.8 FTE Senior Pharmacists 5 [44]. The service is funded by MNHHS. Detailed descriptions of the responsibilities of the OPEN AOS clinical roles are provided in Additional file 1.

Patients of OPEN AOS are older adults residing in RACFs experiencing acute illnesses or injuries. OPEN AOS clinicians provide emergency substitution care via telehealth or in person. Referrals originate from the ambulance service (either from paramedics attending the patient at the RACF or following secondary telephone triage by experienced ambulance service clinicians), General Practitioners (GPs), RACF staff and other local teams providing specialist sub-acute RACF consulting services. Each referral is reviewed by an OPEN AOS clinician who triages the case and determines suitability for OPEN AOS care. Patients not meeting eligibility criteria for the OPEN AOS remain in the care of ambulance services for secondary triage and receive standard clinical review, consideration of referral pathways and standard ambulance attendance.

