## Study design

This pragmatic multi-methods study comprises three discrete but related components: concurrent retrospective quantitative data collection for Components 1 and 2, and prospective qualitative data collection for Component 3. The approach to quantitative and qualitative data collection enables a comprehensive examination of the model’s effectiveness and real-world application. Given the multi-methods design, integration of quantitative and qualitative data through triangulation will not be undertaken. The design is underpinned by the integrated Practical, Robust, Implementation and Sustainability Model (PRISM) and Reach, Effectiveness, Adoption, Implementation and Maintenance (RE-AIM) framework [45]. PRISM will support the identification and description of contextual factors impacting RE-AIM outcomes [45]. This study has been reviewed and approved by the Metro North Human Research Ethics Committee (HREC) B (ECOO168), approval number 102,923. Data storage, retention and disposal will be conducted in accordance with the National Health and Medical Research Council (NHMRC) guidelines [46].

Three components are planned to address the following research questions:

*Component 1*

To what extent (if any) do patient characteristics (such as age, sex, and diagnostic classification^6^) and outcomes differ between OPEN AOS care and standard care (i.e. ambulance attendance with transport to ED care)?Specifically:

4.Primary Outcome: Time to be seen by treating clinician, defined as the amount of time in minutes from the initial contact with QAS to the time seen by either (i) the OPEN AOS clinician (intervention group) or (ii) the ED medical officer (control group).5.Secondary Outcomes:6.Length of care episode, defined as the amount of time in hours from initial contact with QAS to discharge of care.7.Ambulance transport to ED care: defined as the proportion of OPEN AOS patients requiring transport to ED for definitive care.8.ED re-presentation for any cause within 48 h and 28 days of discharge.9.Death within 48 h of discharge.10.Clinical incident^7^ [47] data, defined as clinical incidents that are reported by MNHHS staff that occur within 48 h of discharge.

*Component 2*

Compared to standard care, what is the incremental cost (saving) per person of the OPEN AOS model? 

*Component 3*

How do contextual factors influence implementation and potential future scale and spread of the OPEN AOS model?

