### Inclusion criteria

Intervention: Adults aged 65 years or older who are permanent residents of RACFs situated within the MNHHS district geographical catchment area, with acute care needs and who were referred by the ambulance service to OPEN AOS between 08:00 and 20:00, Monday to Sunday, from 1 July 2022 to 30 June 2023. Patients can receive treatment by OPEN AOS on more than one occasion within the study period.

Control: Adults aged 65 years or older who are permanent residents of RACFs situated within the MNHHS district geographical catchment area, who received standard ambulance attendance and transport to a MNHHS ED between 08:00 and 20:00, Monday to Sunday, from 1 July 2022 to 30 June 2023. Only the first presentation for each patient within the study period will be examined.

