### Exclusion criteria

Patients were excluded if they (1) were assigned emergency status at primary (or secondary) triage (for any clinical reason); (2) did not reside in an RACF or resided in respite care; (3) were attended by ambulance and transported to ED care outside of OPEN AOS model operational hours (i.e. before 08:00 or after 20:00 Monday to Sunday); (4) were referred to OPEN AOS by any referrer other than ambulance services; or (5) received care outside the designated study period (1 July 2022 to 30 June 2023). (6) Patients included in the intervention group, i.e. those seen by OPEN AOS will be excluded from the control group.

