### Data analysis

For our analysis, the comparison of interest is between the intervention and control groups. Re-presentations by patients in either group are not considered as independent events and will be excluded from analyses, however the number of re-presentations during the study period will be noted for the OPEN AOS group. Categorical data will be presented as frequency and percentages, while continuous data will be reported as mean with standard deviation or median with interquartile ranges, depending on the distribution of the data. Categorical data will be analysed using the Pearson Chi-squared test or Fisher’s exact test, and continuous variables using the Student t-test or Mann-Whitney U test. Time to treating emergency clinician and time to discharge from the episode of care will be examined using a generalised linear model or parametric regression model if events are censored e.g., death of a patient. ED re-presentation and mortality will be examined using logistic regression if there are sufficient events. All regression models will be multivariable with fixed effects for triage score, weekend presentation, season, and ambulance referral time. The inclusion of Charlson Comorbidity Index [52] in regression analyses will depend on the extent of missing data. Component 1 will be reported in accordance with the Enhancing the QUAlity and Transparency Of health Research (EQUATOR) guidelines for reporting non-randomised studies [53].

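### The 08:00–20:00 window is set at referral for OPEN AOS but at ambulance attendance and transport for controls, so control eligibility depends on part of the primary outcome

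*Protocol article*

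**What the plan says.** All references are to the protocol article, Component 1.

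- **Inclusion criteria, intervention:** residents "who were referred by the ambulance service to OPEN AOS between 08:00 and 20:00". The anchor is the referral.
- **Inclusion criteria, control:** residents "who received standard ambulance attendance and transport to a MNHHS ED between 08:00 and 20:00". The anchor is attendance and transport.
- **Exclusion criteria, item (3):** removes patients who "were attended by ambulance and transported to ED care outside of OPEN AOS model operational hours", with the limits spelled out as 08:00 and 20:00. The control anchor is therefore stated twice.
- **Study design, primary outcome:** "the amount of time in minutes from the initial contact with QAS to the time seen" by the OPEN AOS clinician or the ED medical officer. Length of care episode starts at the same point.
- **Intervention: the OPEN AOS model:** the service runs 08:00 to 20:00. Ambulance referrals come "either from paramedics attending the patient at the RACF or following secondary telephone triage by experienced ambulance service clinicians".
- **Samples:** matching is on age, sex and diagnosis. Time of day is not a matching variable.
- **Data analysis:** the regression models have "fixed effects for triage score, weekend presentation, season, and ambulance referral time". The last term is not defined for controls, who are not referred to OPEN AOS.

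**The concern.** For a control, the ambulance's arrival and the transport lie between first QAS contact and being seen in the ED. Selecting on their clock time is selecting on part of the outcome. Of two controls who call at 18:30, one attended and transported quickly stays in; one whose ambulance arrives and leaves after 20:00 is excluded, because the wait was long. At the other end, a control who called before 08:00 and was reached after it can enter with a long time, although OPEN AOS was closed at the call.

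At stake are the two time outcomes, which share this starting point, and in particular the comparison by time of day. Adjusting for time of day cannot bring back excluded controls: within a late-call stratum, those kept are the shorter waits.

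**Working it through.** **1. The yardstick.** The plan's own figure comes from Samples: d = 0.2, two-sided alpha 5%, 90% power, 1:3 allocation. Smaller group: n = (1 + 1/3)(1.960 + 1.2816)²/0.2² = 1.3333 × 10.51/0.04 ≈ 350.3, rounded up to 351; controls 3 × 351 = 1053. This reproduces the plan. It does not bear on the window, but it gives 0.2 SD as the scale for judging a shift.

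**2. Inputs for the window.** The article gives no call, response or ED-wait distributions, so the following are assumptions. Intervals are lognormal with log-SD 0.8 (call to attendance), 0.4 (on scene), 0.4 (transport) and 0.9 (ED wait). Medians in minutes, in that order:

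- A: 30, 40, 20, 40
- B: 60, 45, 20, 60
- C: 120, 45, 25, 90

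Four million calls were simulated per scenario. The control mean under each window was compared with the mean for calls made between 08:00 and 20:00.

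**3. Hand check of scenario A.** A lognormal mean is median × exp(s²/2). Call to ED arrival: 30 × 1.377 + 40 × 1.083 + 20 × 1.083 = 41.3 + 43.3 + 21.7 = 106.3 min. Adding the ED wait, 40 × 1.499 = 60.0, gives 166.3 min (simulated 166.2). With a constant call rate, the share of in-window calls reaching ED after 20:00 is about 106.3/720 = 14.8% (simulated 14.7%).

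**4. Late calls (18:00–20:00), constant call rate, window read as requiring ED arrival by 20:00.**

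| Scenario | Lost | Mean time, kept | Mean time, all late callers |
|---|---|---|---|
| A | 79.7% | 136 min | 166 min |
| B | 91.7% | 174 min | 243 min |
| C | 98.0% | 230 min | 376 min |

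This is the strictest reading. If only attendance must fall before 20:00, the losses are 33%, 56% and 79%, and the means of those kept are 153, 202 and 267 min. The distortion is smaller but does not vanish.

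**5. Early calls.** Controls who called before 08:00 but fall inside the attendance-to-arrival window have mean times of 203, 314 and 495 min. They push the control mean upward.

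**6. Shift in the overall control mean (attendance and ED arrival both in the window).**

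| Scenario | 20:00 limit alone | Both limits, constant call rate | Both limits, fewer calls at night |
|---|---|---|---|
| A | −3.1 min (0.04 SD) | −0.6 min (0.01 SD) | −1.7 min (0.02 SD) |
| B | −11.3 min (0.09 SD) | −0.8 min (0.01 SD) | −6.4 min (0.05 SD) |
| C | −41.6 min (0.19 SD) | −1.6 min (0.01 SD) | −21.4 min (0.10 SD) |

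With a constant call rate, the long waits lost at 20:00 are almost exactly replaced by those gained at 08:00. With fewer night calls the replacement is incomplete. As a check, a night call rate of 60% or 30% of the day rate gave shifts of −1.6 to −23.2 min (0.02 to 0.11 SD). These figures concern the control mean only; cutting by the OPEN AOS window was not modelled.

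**The case against.** The strongest reply is that the intervention group is also restricted after time zero. Referral follows first contact, and when paramedics refer from the scene it is close to the control's attendance. The Samples section describes the OPEN AOS patients as treated within operating hours, so late callers with long waits may drop out there too. This stands: the groups differ in degree, and part of the distortion may be common to both.

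The wording of exclusion (3) also does not settle a case that straddles a limit, such as attendance at 19:30 and departure at 20:10, or say whether transport means departure or ED arrival. The number of controls lost is therefore not fixed by the text. This stands too, and is itself something to repair. The ED wait, a further part of the outcome, is not restricted by the window.

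A reader might infer that the primary comparison is biased by a known amount in a known direction, because long-wait controls are cut out. The documents do not support that. The 08:00 limit works the other way and can nearly cancel the loss, and every delay and call rate above is assumed.

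Adjustment for ambulance referral time and the general acknowledgement of selection bias under Limitations do not answer the point. The first cannot restore excluded patients. The second concerns the lack of randomisation, whereas this selection comes from an eligibility rule that can be changed.

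**Conclusion.** The point holds as a flaw in the eligibility rule. The window is tied to different events in the two groups, and for controls those events lie inside the primary outcome. Nothing in the matching or the models undoes this.

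Its effect on the result is not established. Under the assumed delays and call patterns, the overall control mean moves by about 0 to 0.1 SD toward shorter times, up to about half the design effect of 0.2 SD. Taken alone, that would understate any advantage of OPEN AOS. The net effect on the comparison could be smaller, because the OPEN AOS window may shorten times in that group as well. Among late-day calls the distortion of control times is larger, and how large depends on how straddling cases are read.

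**What to change.** Select both groups on the dispatch-system (CAD) time of first QAS contact, within the same window. Remove attendance and transport time from the control inclusion criterion and from exclusion (3). This also settles the straddling cases.

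That change alone could tilt the comparison the other way: late callers reach OPEN AOS only if handled before closing, while long-wait controls would all be kept. So either end the call window for both groups at a common time sufficiently before 20:00, chosen before outcomes are compared, or add a sensitivity analysis that omits calls near 08:00 and 20:00. In the models, define the time-of-day term as the time of first QAS contact in both groups.

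The cost is small. The design is retrospective, and QAS time stamps are already listed among the data sources in Table 1. Some cases near opening and closing will enter or leave the sample. The article does not allow that number to be calculated, so the size of the intervention group should be checked against the required 351 after the change.

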## Setting

The study is set in the Metro North Hospital and Health Service (MNHHS) district in south-east Queensland, Australia [35]. In 2024, the MNHHS region had 87 RACFs (85 non-government) with 9417 RACF beds. The district is serviced by five public hospitals; four are classified as large or very large and one is classified as small. The EDs within each of the five hospitals vary in their level of service capability and capacity [36, 37].

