### Samples

In the 12-month study period from 1 July 2022 to 30 June 2023, approximately 7600 ED presentations from RACFs arrived by ambulance to district’s ED sites. During that same period, 735 patients were treated by OPEN AOS during their operational hours (08:00–20:00) Monday to Sunday. Patients treated in the Intervention group will be matched with up to three randomly selected control group patients without replacement with matching on age (+/- 5 years), and exact matching on sex and diagnostic classification section (or chapter if diagnoses are uncommon) as per the International Classification of Diseases, 10th Revision Australian Modification (ICD-10-AM) using the ‘R’ package Matching: Multivariate and Propensity Score Matching with Balance Optimization [50]. Groups sizes of 351 for the intervention group and 1053 for the control group will achieve 90% power to reject the null hypothesis of no effect on the time to be seen by treating clinician when there is a Cohen’s d small effect size of 0.2 using a two-sided, two-sample test assuming equal variance and an alpha of 5% [51].

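### The two arms choose the index episode by different rules and controls are dropped for OPEN AOS use at any time, which can bias ED re-presentation against OPEN AOS

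*Protocol article*

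**What the plan says.** Four statements in the Protocol article, all under Component 1, together fix the index episode.

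- **Control arm** (Inclusion criteria): "Only the first presentation for each patient within the study period will be examined". The presentation must be an ambulance transport to an ED in the district between 08:00 and 20:00.
- **Intervention arm** (Inclusion criteria): an ambulance referral to OPEN AOS between 08:00 and 20:00. "Patients can receive treatment by OPEN AOS on more than one occasion within the study period". Nothing requires the episode to be the resident's first acute episode of the year.
- **Exclusion criterion (6)**: "Patients included in the intervention group, i.e. those seen by OPEN AOS will be excluded from the control group". No time limit is given, so OPEN AOS use after the control presentation also disqualifies.
- **Data analysis**: "Re-presentations by patients in either group are not considered as independent events and will be excluded from analyses". Read with the Inclusion criteria, this makes the intervention index the first OPEN AOS episode.

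The outcome at issue is the secondary outcome "ED re-presentation for any cause within 48 h and 28 days of discharge" (Study design). Component 2 takes its re-presentation figures from Component 1. The matching variables (age, sex, diagnosis) and the listed covariates (triage score, weekend, season, referral time) do not include prior ED or ambulance use. The Charlson index enters only if missing data allow.

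**The concern.** A resident with many acute episodes has more chances that at least one goes to OPEN AOS. Under these rules such a resident enters the intervention arm, even if several ED visits came before, and leaves the control arm, even if the OPEN AOS visit came after the control presentation. The second step makes eligibility of a control depend on events after the index date. The intervention arm is then weighted towards frequent presenters and the control arm towards infrequent ones.

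Frequent presenters are more likely to be back in ED within 28 days whatever care they received. At stake are an outcome that bears on safety and the incremental cost per patient, from which savings are modelled for all 87 facilities.

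**Working it through.** **The plan's own figure.** For d = 0.2, two-sided 5%, 90% power and 1:3 allocation, the smaller group is (1.960 + 1.282)² × (1 + 1/3) / 0.2² = 350.2, so 351, with 1053 controls. Power is 90.1% by the normal approximation and 90.0% by the noncentral t. The figure reproduces, and it concerns the primary outcome only.

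**Inputs from the Protocol article.** "approximately 7600 ED presentations from RACFs arrived by ambulance to district’s ED sites" and "735 patients were treated by OPEN AOS during their operational hours" over 12 months (Samples); "the MNHHS region had 87 RACFs (85 non-government) with 9417 RACF beds" (Setting).
- Episodes per bed-year: m = (7600 + 735)/9417 = 0.885.
- Share of episodes to OPEN AOS: a = 735/8335 = 0.088.
- Share to ED: e = 7600/8335 = 0.912.

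**Assumptions not in the documents.**
- 60% of ED presentations fall in hours, so the share that can be a control index is b = 0.6 × 7600/8335 = 0.547.
- Residents' rates are gamma-distributed, with relative variance v from 0 to 2.
- Episodes follow a Poisson process. The route is independent of the resident and has no effect on later episodes.
- There is no mortality, matching or covariate, and the 28 days run from the index contact.

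**Formulas.** Let L(s) = (1 + s·m·v)^(−1/v), the mean of exp(−sλ) over residents' rates λ, and r = e × 28/365 = 0.0699. Under the plan's rules:
- Intervention (at least one OPEN AOS episode): [1 − L(a) − L(r) + L(a+r)] / [1 − L(a)]
- Control (at least one in-hours ED presentation, no OPEN AOS episode all year): [L(a) − L(a+b) − L(a+r) + L(a+b+r)] / [L(a) − L(a+b)]

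**Numbers for v = 1.** L(a) = 0.92761, L(r) = 0.94171, L(a+r) = 0.87724, L(a+b) = 0.64012, L(a+b+r) = 0.61572.
- Intervention: 0.00792/0.07239 = 10.9%
- Control: 0.02597/0.28749 = 9.0%
- Odds ratio: (0.1094/0.8906)/(0.0903/0.9097) = 1.24, with no true effect

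**Range.** Scenario A is the one above. Scenario B treats all ED presentations as eligible (rate 0.9, share to OPEN AOS 0.09). Scenario C assumes half fall in hours and counts only those: (3800 + 735)/9417 ≈ 0.5 and 735/4535 = 0.16. B and C use the same formulas with b = e = 1 − a.

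| v | A: intervention v control | A: OR | B: OR | C: OR |
|---|---|---|---|---|
| 0 | 6.0% v 6.0% | 1.00 | 1.00 | 1.00 |
| 0.33 | 7.8% v 7.2% | 1.09 | 1.13 | 1.08 |
| 0.5 | 8.6% v 7.7% | 1.13 | 1.18 | 1.11 |
| 1 | 10.9% v 9.0% | 1.24 | 1.34 | 1.21 |
| 2 | 15.1% v 11.0% | 1.43 | 1.60 | 1.39 |

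A simulation of 400,000 residents agrees: in B at v = 2 it gave 15.6% v 10.2% (OR 1.63), and in C at v = 2 it gave 1.37.

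**Which rule contributes what.** Without criterion (6) the control risk is [1 − L(b) − L(r) + L(b+r)]/[1 − L(b)]. In A the odds ratio at v = 2 falls from 1.43 to 1.27, so the index rule accounts for more than half of the gap and both rules must change. In the simulations of B and C at v = 1 to 2, about 28% to 50% of intervention index episodes followed an ED presentation that year.

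**One common rule.** Index each resident at the first eligible episode and classify by route. The chance of each route is then the same at every rate and cancels. Both arms have risk [1 − L(a+b) − L(r) + L(a+b+r)]/[1 − L(a+b)], which at v = 1 in A is 0.03389/0.35988 = 9.4%. The odds ratio is exactly 1.

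**Chance of a false signal.** With 351 v 1053, an unadjusted comparison would reject against OPEN AOS with probability 19% (v = 1) to 52% (v = 2) in A, against a nominal 2.5% in that direction. At v = 0.33 it is 6%.

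**The case against.** - **The analysis already takes one episode per patient.** This stands. A reader might infer from the sentence on repeat treatment that all OPEN AOS episodes are compared with first presentations only. The Data analysis section rules that out by excluding repeats in either group. What remains is a first OPEN AOS episode, possibly after ED visits, against a first ED presentation.
- **Criterion (6) has a purpose.** It keeps the groups disjoint for a two-sample comparison and for matching without replacement. True, but one index episode per resident does that without using later events.
- **The size rests on assumptions.** This stands. The spread of rates and the in-hours share are not in the documents. The 735 are not stated to be ambulance referrals only, and the 7600 are not stated to omit emergency-status cases. With identical rates there is no bias.
- **The calculation omits the plan's controls.** Matching on age, sex and diagnosis, the covariates, and Charlson if used, would remove the part of the variation in rates that they explain. None of them records prior use, so some bias is likely to remain.
- **OPEN AOS clinicians triage for suitability.** This is not modelled and could act in the other direction, so the sign of the net bias from all sources is not known.
- **The Limitations section discloses selection bias.** It does so in general terms. This part arises from the plan's own rules and can be removed.

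**Conclusion.** The point holds in a conditional form. As written, the two arms have different index rules, and a control can be removed for something that happens after the index date. If residents differ in their rate of acute episodes, which is to be expected in this population but is not quantified in the documents, 28-day ED re-presentation is pushed against OPEN AOS. The unadjusted odds ratio is about 1.1 to 1.4 for relative-rate variance of about 0.3 to 2, up to 1.6 under other assumed rates. The same mechanism applies at 48 hours, which was not calculated.

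The effect is shown for a secondary outcome and the cost model that uses it. A reader might infer that the primary comparison of time to clinician is biased too; nothing here shows that, and its sample size is correct. Nor is the difference in the 08:00–20:00 window (referral time in one arm, attendance and transport in the other) shown to cause bias of any size. It is an inconsistency to tidy.

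**What to change.** Use one index rule in both arms. Either:

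1. **First eligible episode.** Take each resident's first eligible ambulance episode in the study period and classify it by the route taken then (OPEN AOS or ED). Delete criterion (6) as a condition on later use.
2. **All eligible episodes.** Include every eligible episode in both arms, with resident-clustered standard errors and no exclusion for OPEN AOS use before or after. Keeping an exclusion for earlier OPEN AOS use in controls only would leave a one-sided rule, so it should go as well.

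In either case, define the 08:00–20:00 window by the same time stamp in both arms, namely initial ambulance contact, and align the Inclusion criteria sentence on repeat treatment with the Data analysis section.

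The cost is wording and programming on data already due to be linked. Option 1 loses the OPEN AOS episodes that follow an eligible ED presentation. If half were lost, the upper end of the share above, 735 × 0.5 ≈ 368 would remain before other exclusions, only just above 351, so the count should be checked before choosing. Option 2 loses none but needs clustered errors.
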